### Participants

Participants in the data collection in both arms of the study are children attending the local primary school. The study has no specific exclusion criteria; all children enrolled in the local primary school are eligible for participation, provided a parent or guardian is available to provide informed consent.

Prior to the baseline field visit, teachers were asked to organise a parent meeting at the school on the day the research team arrived. At this meeting, the study was explained in detail to the parents by the Timorese project manager. Parents were provided with both written and schematic information sheets and given the opportunity to ask questions about the study prior to providing written informed consent.

At baseline, informed consent was obtained for 522 out of 602 eligible children (i.e. those who were enrolled in the local primary school), representing a recruitment rate of 87%. Of the 80 children who were not recruited to the study, 39 were absent from school during the baseline visit, and 41 were present but their parents were unable to attend the school to provide informed consent. No refusals of consent were recorded among children whose parents attended.

At the 6-month follow-up visit, which will take place in a new academic year, teachers will again be asked to arrange a parent meeting, and consent will be sought from any parents who did not attend at baseline, as well as from parents of children who are new to the school, including all children in the new grade 1 cohort.

### Data collection

#### Questionnaires

Study participant questionnaires are administered as interviews at both baseline and follow-up. They are conducted by trained local fieldworkers and include two components. The first component consists of questions asked directly to the children, relating to diarrhoea history, access to deworming medications, presence and use of a household latrine, defecation practices, handwashing practices and shoe wearing at home, at school and while defecating. The second component consists of questions directed to the caregiver, relating to household water source, household assets, education and occupation. Questionnaires are also administered to school and village leaders and include questions relating to school and community latrines and water sources.

#### Stool samples

Stool samples are collected at both baseline and 6-month follow-up. On the first day of each field visit, all participating children are given an explanation of the study and requested to provide a stool sample as part of their participation. Each child is given a labelled plastic container and provided with instructions on the collection of a faecal sample, ideally to be done the following morning and returned to the field team at the school.

Upon receipt of the stool specimens by the field team, two aliquots of 2–3 g are taken and preserved in 15-mL centrifuge tubes—one containing 8 mL of 10% formalin, and the other containing 5 mL of 5% potassium dichromate.

The formalin-fixed samples are transported to the University of Melbourne, Victoria, Australia, for diagnostic processing using microscopy. This is achieved using a simple sodium nitrate flotation technique and direct microscopy to quantify the number of STH eggs (*A. lumbricoides*, hookworm spp. and *T. trichiura*) in each faecal sample [66].

The potassium dichromate-fixed samples are sent to the QIMR Berghofer Medical Research Institute, Brisbane, Australia, for diagnostic processing using a polymerase chain reaction (PCR) technique. DNA is extracted using the PowerSoil DNA extraction kit, with modifications [67], and a real-time multiplex PCR is then undertaken to detect and quantify soil-transmitted helminths (*Ascaris* spp., *N. americanus*, *Ancylostoma* spp. and *T. trichiura*) [68].

#### Measurement of height, weight and haemoglobin

At both baseline and follow-up field visits, all children for whom informed consent has been provided undergo measurement of height (to the nearest 0.1 cm) and weight (to the nearest 0.5 kg), obtained as a single measurement. A fingerprick blood sample is also obtained for measurement of haemoglobin. These measurements are done by the (S)WASH-D for Worms field team, which includes a nurse, utilising a portable height rod (Wedderburn, WSHRP), digital scale (Livingstone, SCLBATHDIG) and a portable haemoglobin analyser (Hb 201+, HemoCue, Angelholm, Sweden).

Height and weight measurements will be used, along with age, to calculate anthropometric values indicative of nutritional status in children: weight-for-age, height-for-age, weight-for-height and BMI-for-height. These will be calculated as *Z*-scores, the number of standard deviations from the mean of the standard population, with malnutrition and severe malnutrition defined as values 2 and 3 standard deviations, respectively, below the mean score of the standard population [69], using the 2006 WHO database for child growth standards [70]. Anaemia is defined as per the WHO classification guidelines, adjusted for altitude in communities more than 1000 m above sea level.

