### Study outcomes

The primary outcomes will be used to examine feasibility and acceptability (objective 1). Primary outcomes relating to study feasibility and acceptability in terms of recruitment and participation (objective 1A) are as follows: the proportion of eligible children whose parents provide informed consent; the proportion of eligible children who provide stool samples, complete questionnaires and undergo measurement of height, weight and haemoglobin; and the retention rate of participants between baseline and follow-up.

Primary outcomes relating to the feasibility and acceptability of the WASH and deworming programmes (objective 1B) are as follows: the proportion of children and eligible community members who receive albendazole; the time taken for the completion of the school WASH programmes in each study cluster; the time taken to achieve 80% household latrine coverage in each intervention cluster; the proportion of schools and households with latrines and access to a reliable source of improved water; the proportion of schools with handwashing stations; and the proportion of children who report using latrines and handwashing stations.

Secondary outcomes, which will be used to inform sample size calculation (objective 1D) and to examine the study hypothesis (objective 2), are as follows: 6-month cumulative incidence of infection with STH (*Ascaris* spp., *N. americanus*, *Ancylostoma* spp. and *T. trichiura*) at follow-up; mean intensity of STH infection (measured as average number of eggs per gramme of faeces) at follow-up; mean haemoglobin concentration; and four anthropometric indices: weight-for-age, height-for-age, weight-for-height and body mass index (BMI)-for-age *Z*-scores (to identify underweight, stunting, wasting and thinness, respectively). Cumulative incidence of STH infection is the planned primary outcome in the full-scale trial. It should be noted that the term “cumulative incidence” is used for simplicity, as cases diagnosed at follow-up will include both incident infections and prevalent infections not cured by albendazole, particularly in the case of hookworm and *T. trichiura* infections [65].

All outcomes (see Table 1) will be compared between control and intervention clusters.

**Table 1 Tab1:** Study outcomes

Primary outcomes	
Proportion of eligible children who:	Provide parental informed consent
	Provide stool samples
	Complete questionnaires
	Undergo measurement of height, weight and haemoglobin

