Participant retention rates between baseline and follow-up (defined as the proportion of baseline participants who were retained in the study at follow-up)	
Proportion of children and eligible community members who take albendazole	
Time taken to complete school WASH programmes in each study cluster	
Time taken to achieve 80% household latrine coverage in each intervention cluster	
Proportion of schools and households with functional and clean latrines	
Proportion of children who report using household and school latrines	
Proportion of schools and households with access to a reliable primary source of improved water	
Proportion of schools with handwashing stations	
Proportion of children who report using handwashing stations at school	
Secondary outcomes	
Cumulative incidence of infection with:	*Ascaris* spp.
	*T. trichiura*
	*N. americanus*
	*Ancylostoma* spp.
Mean intensity of infection (calculated as the average number of eggs per gramme of faeces) of:	*Ascaris* spp.
	*T. trichiura*
	*N. americanus*
	*Ancylostoma* spp.
Mean haemoglobin concentration	
Weight-for-age (underweight) *Z*-score	
Weight-for-height *Z*-score (wasting)	
Height-for-age *Z*-score (stunting)	
Body mass index (BMI)-for-age *Z*-score (thinness)	

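### The anthropometry rule computes BMI-for-height where the listed outcome is BMI-for-age, and it names one growth reference without showing that it covers primary-school children

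*Protocol article*

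**What the plan says.** The Study outcomes section of the Protocol article lists four anthropometric secondary outcomes, all Z-scores: "weight-for-age, height-for-age, weight-for-height and body mass index (BMI)-for-age". It ties the fourth to thinness. Table 1 repeats that index as "Body mass index (BMI)-for-age", again labelled thinness.

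The section on measurement of height, weight and haemoglobin is the only place that says how the scores are obtained. It states that "Height and weight measurements will be used, along with age, to calculate anthropometric values", and then names the indices as "weight-for-age, height-for-age, weight-for-height and BMI-for-height". It takes malnutrition and severe malnutrition as 2 and 3 standard deviations below the reference mean, "using the 2006 WHO database for child growth standards". No second reference is named.

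On who is measured, the Participants section says that "all children enrolled in the local primary school are eligible for participation" if a parent or guardian can consent, and it sets no age limit. At baseline, "informed consent was obtained for 522 out of 602 eligible children". At follow-up, consent is sought for further children, "including all children in the new grade 1 cohort".

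The Analysis section reports the mean and standard deviation of the four Z-scores and models them by mixed effects linear regression. The objectives at the end of the Background include initial estimates of nutritional indicators to inform the full trial's sample size.

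**The concern.** There are two separate problems in the same sentence of the calculation rule.

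First, the rule and the outcome list disagree on the fourth index. BMI-for-age compares a child's BMI with that of children of the same age; an index indexed on height is a different quantity. An analyst who followed the measurement section literally would not produce the thinness outcome in Table 1.

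Second, a Z-score exists only where the reference has values for a child of that age or height. The article describes its target population as school-aged, yet fixes one reference, a set of child growth standards, without saying which ages or heights it covers. If coverage ends near the age at which children start school, most scores would be missing or extrapolated. The children with valid scores would then be the youngest in each school rather than a cross-section of it. The means, standard deviations and malnutrition proportions would describe that subgroup, while the full trial would be planned for the whole school.

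**Working it through.** No sample size or power formula bears on this point, and the article gives no figure to reproduce. The check is a comparison of sections, followed by what can be said about size.

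**Step 1: index names.**

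| Index | Study outcomes text and Table 1 | Measurement section |
|---|---|---|
| 1 | weight-for-age | weight-for-age |
| 2 | height-for-age | height-for-age |
| 3 | weight-for-height | weight-for-height |
| 4 | BMI-for-age (thinness) | BMI-for-height |

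Three of four agree and one does not. Two places give BMI-for-age and one gives BMI-for-height. The measurement section itself says that age enters the calculation. The natural reading is that BMI-for-age is intended and the measurement section contains a slip. The Analysis section does not settle it, because it refers only to four anthropometric indices without naming them.

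**Step 2: reference against population.** The reference is the 2006 WHO child growth standards, for all four indices. The population is everyone enrolled at the primary school, with no age bounds. The article treats preschool-aged children as a separate group (Background, Discussion), and the national stunting figure in the Setting section is for children under 5. By its own description, then, the sample is of school age, and no reference is identified as covering school age.

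**Step 3: how many children are affected.** Let p be the share of baseline participants outside the reference's range for a given index. The number without a valid score is 522 × p. The article reports neither the children's ages nor the range of the standards, so p is unknown:

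- p = 0 gives 522 × 0 = 0 children
- p = 0.5 gives 522 × 0.5 = 261 children
- p = 1 gives 522 × 1 = 522 children

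If the standards are assumed to stop at about 5 years, p would be close to 1 for a primary-school sample. That cut-off comes from outside the article.

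**Step 4: direction of the distortion under that assumption.** Children with valid scores would be those below the cut-off, the youngest. The gap could also differ between visits. Baseline precedes the WASH programme and follow-up comes 6 months after albendazole, so each baseline child is more than 6 months older at follow-up and fewer would fall under any age limit. Meanwhile a new grade 1 intake joins. The scored groups at the two visits would then not be comparable.

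**The case against.** The strongest reply has three parts.

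*The BMI wording is trivial.* The outcome text, Table 1 and the mention of age all point to BMI-for-age. This stands as to intent. It does not remove the need for correction, because the only statement of the calculation names the wrong index.

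*The coverage problem rests on facts outside the article.* The age and height limits of the standards are not stated, the cited source is not available for checking, and no participant ages are reported. Coverage may also differ by index: one defined on height rather than age could be limited by height, so some older but short children might still be scored. This stands too, and it limits the conclusion. What the article does show is a single named reference, a school-aged sample, and nothing linking the two.

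*The consequences are modest.* Anthropometry is secondary here, the Discussion says the pilot is not powered for secondary outcomes, and the full trial's planned primary outcome is cumulative incidence of infection. Heights and weights are kept in the database and age is available, so scores can be recomputed on another reference. All true, and nothing irrecoverable has been fixed. But lack of power to compare arms does not excuse the estimates themselves, since nutritional estimates are a stated product of the pilot.

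A reader might go further and infer that the two problems together make the listed Z-scores impossible to produce validly for most participants. The article does not support that. The BMI slip leaves the other three indices untouched, and the claim about most participants depends wholly on the assumed age limit.

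**Conclusion.** The contradiction between BMI-for-height in the measurement section and BMI-for-age in the outcome list is established from the article alone. It affects one of four anthropometric outcomes and should be corrected.

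The reference question holds conditionally. One reference is fixed for a primary-school sample without stated coverage. Assuming the standards end at about 5 years, most of the 522 baseline children would lack a valid score and the estimates would describe the youngest few. Without that assumption, the affected share can only be bounded between 0% and 100%. It would also be too strong to conclude now that any particular index must be dropped or capped at a given age, because that depends on limits the article does not give.

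The point deserves action before analysis because the Z-score means and standard deviations are meant to inform the full trial. It does not touch the primary feasibility outcomes or the infection outcomes.

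**What to change.** 1. In the measurement section, change BMI-for-height to BMI-for-age, so that the calculation rule matches the Study outcomes section and Table 1.
2. For each of the four indices, check the age and height range of the named reference against the ages and heights of the enrolled children, and state that range.
3. Score children outside the range on a WHO reference that covers school age, and name it alongside the present one.
4. Where no reference covers the enrolled children for an index, restrict that index to those who are covered, or remove it from the outcome list with the reason given.
5. Report the number of children scored for each index at each visit.

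The cost is a wording change and a different reference file for the calculation. Height, weight and age are already collected, so nothing has to be measured again. One or two secondary indices may be restricted or lost, depending on what step 2 shows.

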### Data management and confidentiality

Questionnaire data, as well as height, weight and haemoglobin measurements and results of parasitological examinations, are entered into a password-protected database. Data are entered twice by two different data clerks, and the database has in-built range checks for appropriate variables. The final study dataset will be accessible only by the study investigators. Original questionnaires are kept in a locked cabinet in the study office in Timor-Leste and will be destroyed after 7 years. Stool samples are labelled using the participant’s unique study ID number, with no identifying information. Results of the parasitological examinations are entered into the study database described above.

### Analysis

For the primary outcomes, analyses will be mainly descriptive. The proportions of eligible participants who gave informed consent and participated in each aspect of data collection will be calculated (with 95% confidence intervals (CIs)) and compared across the two study arms, at both baseline and follow-up, and will also be examined separately by gender and age group. The proportion of baseline participants retained at follow-up will also be calculated and compared across the study arms. Descriptive statistics will be used to examine the completeness of data collected using the study questionnaires.

The proportion of children and eligible community members who received albendazole, the proportion of schools and households with access to various WASH components and the proportion of children who report using various WASH components will be calculated (with 95% CIs) and compared across the two study arms, at both baseline and follow-up. The time taken to complete the school and community WASH programmes will be examined using descriptive statistics (mean, median, range).

For the secondary outcomes, prevalence at baseline and cumulative incidence at follow-up will be calculated (with 95% CIs) for each STH as will the mean and standard deviation of the infection intensity, expressed as eggs per gramme of faeces. Mean and standard deviation of the haemoglobin concentration and *Z*-scores for the four anthropometric indices will also be calculated. These outcomes will be compared across both arms of the trial using mixed effects multivariable regression models that account for clustering of participants within schools and villages. Cumulative incidence of infection will be modelled using multivariable Bernoulli logistic regression, with age and sex entered as covariates, baseline infection status as a fixed effect, and school and village as random effects. The study arm will be entered as a binary fixed effect to estimate differences in cumulative incidence between the study arms, using a cumulative incidence ratio (CIR). Intensity of infection will also be modelled with random and fixed effects as described above. Mixed effects linear regression will be used to model anthropometric *Z*-scores and mean haemoglobin concentration. Stata software will be used for all analyses (StataCorp LP, College Station, TX).

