**Methods:**

The (S)WASH-D for Worms pilot is a two-arm, non-randomised cluster intervention study. The aims are to determine feasibility and acceptability of the intervention and study procedures and to establish proof of principle for the hypothesis that STH control programmes directed to the entire community will lead to greater reductions in STH infections in children than programmes directed only to school-aged children. Of the six participating communities, three receive a school-based integrated WASH and deworming programme and three additionally receive a community-based integrated WASH and deworming programme. The primary outcomes are the proportions of eligible children who enrol in the study and participate in the data collection, and outcomes relating to WASH and deworming programme completion, coverage, and use. Secondary outcomes are the cumulative incidence and mean intensity of STH infection in school-aged children at 6-month follow-up, mean haemoglobin concentration and several anthropometric indices. Results will inform the design of a cluster-randomised controlled trial (RCT).

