## Methods

### Design

This pilot study is a two-arm, non-randomised cluster intervention study. The six participating clusters, each based around a local primary school, are located in Aileu and Manufahi municipalities of Timor-Leste. Three clusters comprise the “control” arm of the study: in these, a WASH programme is delivered to the primary school, and albendazole is distributed to the schoolchildren. The other three clusters comprise the “intervention” arm, in which a WASH programme is delivered to both the primary school and the community in which the school is located, and albendazole is distributed to all community members. The follow-up period for the pilot study is 6 months following the distribution of albendazole, which will allow sufficient time for STH reinfection to occur [24], and represents the follow-up interval planned for the full-scale trial, which will take place over a 2-year period. Figure 1 depicts a flow diagram for the pilot study. This pilot study is registered with the Australian New Zealand Clinical Trials Registry (registration number ACTRN12615001012561).

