## Discussion

The current WHO guidelines for STH control focuses strongly on school- and preschool-aged children, who experience the highest burden of disease-related morbidity. In the context of significant global interest in the control of neglected tropical diseases, including significant donations from pharmaceutical companies, and recognition of the potential added benefit of WASH interventions for sustainable control, there is increasing interest in the optimal control strategies for STH.

The (S)WASH-D for Worms pilot study primarily represents a feasibility study in preparation for a cluster-randomised controlled trial (RCT) investigating the differential impact of school- and community-based integrated STH control programmes. The integrated control programme implemented in the study includes both deworming medications, distributed by the research team, and a water, sanitation and hygiene intervention, implemented by partner NGOs. The pilot study will provide an indication of the rate of recruitment and participation which could be expected in a full-scale RCT, which will be used to inform sample size calculations for the full-scale trial. The pilot study will also provide an opportunity to test the study procedures and data collection forms and to examine the feasibility and acceptability of the deworming and WASH programmes, in particular, the time frames for completion of the WASH programmes and their ability to achieve improved WASH access and use. Furthermore, it will allow for the identification of operational challenges involved in implementing such a trial in a developing country. In particular, the pilot study will give an estimation of the time frames required for the completion of the school- and community-based WASH interventions.

The pilot study sample size does not allow sufficient power to detect significant differences in secondary outcomes between study arms. Initial estimates of the secondary outcomes obtained in this pilot study will be used to provide preliminary evidence for our study hypothesis that a community-wide intervention is more effective at reducing STH infections in children than a school-based intervention and to inform sample size calculation. Results of hypothesis testing will be interpreted with caution; emphasis will be given to confidence intervals, rather than *p* values, and results will be presented in terms of assessment of “proof of principle”, rather than establishment of causation.

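### With three clusters per arm, the mixed-model arm contrasts need a named small-sample method, because proof of principle will be read from their confidence intervals

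*Protocol article*

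**What the plan says.** The Design section fixes the structure: "The six participating clusters, each based around a local primary school". The abstract gives the split: "Of the six participating communities, three receive a school-based integrated WASH and deworming programme", and the other three receive the community programme as well. Allocation was not randomised.

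For the secondary outcomes, the Analysis section specifies "mixed effects multivariable regression models that account for clustering of participants within schools and villages". Infection is modelled by Bernoulli logistic regression, and haemoglobin and Z-scores by linear regression. Arm is a binary fixed effect and school and village are random effects; the infection model adjusts for age, sex and baseline infection and is to yield a cumulative incidence ratio. Stata is named. No estimation method, degrees of freedom or small-sample correction is given.

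On reading these results, the Discussion says that "emphasis will be given to confidence intervals, rather than" *p* values, and that they will be presented as an assessment of proof of principle. The same paragraph concedes low power for the secondary outcomes, promises caution with hypothesis tests and disclaims causation.

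On the primary outcomes, the Analysis section says "For the primary outcomes, analyses will be mainly descriptive". The consent and participation proportions "will be calculated (with 95% confidence intervals (CIs)) and compared across the two study arms". Clustering is mentioned only for the secondary outcomes. The Participants section reports one such proportion: "informed consent was obtained for 522 out of 602 eligible children", stated as 87%.

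**The concern.** Arm varies only between clusters. However many children are measured, the arm contrast rests on six school-level results, with 6 - 2 = 4 degrees of freedom. A mixed model estimates the between-school variance from those same six units. If the interval is then built with a normal critical value, it ignores the uncertainty in that variance; under maximum likelihood the variance is also biased downwards. Both effects make the interval too narrow.

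This matters because the article directs readers to the intervals. The stated caution concerns power and *p* values and does not widen an interval. An interval that excludes no effect more often than 5% of the time under the null could be presented as proof of principle for the full trial. Infection, the outcome most affected, is that trial's planned primary outcome.

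There is a smaller, related point. Recruitment and participation rates are to inform the full trial's sample size, and an interval that treated 602 children in six schools as independent would overstate how well those rates are known.

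**Working it through.** **Inputs**
- Clusters: 6, three per arm (abstract; Design).
- Children: 602 eligible, 522 consented (Participants). Per school: 602/6 = 100.3 and 522/6 = 87.
- Base rate of infection: 29% in school-aged children nationally (Setting), rounded to 30%.
- ICC: not in the article. Assumed, and shown as a range.

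**1. The article's own figure.** 522/602 = 0.867, which rounds to 87%. The reasons given for non-recruitment, 39 + 41 = 80, match 602 - 522 = 80. The figure reproduces.

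**2. What theory predicts when between-school variance dominates.**
- t(4) at 0.975 is 2.776, against z = 1.960; the ratio is 1.42. P(|t4| ≤ 1.96) = 0.878, so REML with z should cover about 88%.
- ML divides the between-cluster sum of squares by 6, not 4, so the standard error shrinks by √(4/6) = 0.816. The effective cut-off is 1.96 × 0.816 = 1.60, and P(|t4| ≤ 1.60) = 0.815, so ML with z should cover about 82%.
- A t(4) interval is then wider than ML with z by 1.42 × √(6/4) = 1.42 × 1.22 = 1.73.

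**3. Linear outcomes, simulated** (3 v 3 clusters of 87, no true effect, 40,000 runs per row). Coverage of nominal 95% intervals:

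| ICC | ML, z | REML, z | Cluster means, t(4) |
|---|---|---|---|
| 0 | 95.5% | 96.3% | 95.0% |
| 0.01 | 89.1% | 92.0% | 95.0% |
| 0.02 | 85.8% | 90.1% | 95.0% |
| 0.05 | 82.8% | 88.4% | 94.9% |
| 0.10 | 82.1% | 88.2% | 95.1% |

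**4. Infection, simulated** (random-intercept logistic model by ML, Wald z interval for the arm log-odds ratio, 30% incidence, no true effect). ICC is on the latent scale: school variance = ICC/(1 - ICC) × π²/3.

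| Latent ICC | 80 per school, 1,000 runs | 87 per school, 600 runs |
|---|---|---|
| 0.02 | 90.5% | 89.0% |
| 0.05 | 84.7% | 83.5% |
| 0.10 | 80.2% | 81.5% |

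Monte Carlo error is about √(0.85 × 0.15/1000) = 1.1 points and √(0.84 × 0.16/600) = 1.5 points, so the two columns agree. In the first setting, a t(4) interval on the six school log-odds covers 95.9%, 95.2% and 94.1%, and its median width is 1.67 to 1.70 times that of the Wald interval.

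**5. Consent proportion.**
- Unclustered: SE = √(0.867 × 0.133/602) = 0.0138. The 95% CI is 0.867 ± 1.96 × 0.0138 = 84.0-89.4%.
- Clustered: design effect = 1 + (100.3 - 1) × ICC, with t(5) = 2.571 for six clusters.
  - ICC 0.02: design effect 2.99, CI 80.6-92.9%.
  - ICC 0.05: design effect 5.97, CI 78.0-95.4%.

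The ICC in step 5 is on the proportion scale and is not the latent ICC of step 4. Latent 0.05 means a school variance of (0.05/0.95) × 3.29 = 0.173. At 87% that is about 0.867 × 0.133 × 0.173 = 0.020 on the proportion scale, a design effect near 3.

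**The case against.** The strongest reply is that the article never says the intervals will be z-based. It fixes mixed-effects regression in Stata, and a condensed article may leave estimation and degrees of freedom to an analysis plan that is not shown. That stands: a reader might infer that the intervals will be too narrow, but the text supports only that they will be if ordinary inference is used. For haemoglobin and Z-scores, REML with Kenward-Roger would be compatible with the stated model. The reply is weaker for infection, because that correction is a linear-model tool and does not carry over directly to the Bernoulli model.

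Other stronger readings also go beyond the document:
- *The primary-outcome intervals ignore clustering.* This is read from silence and from the contrast with the secondary outcomes. The analysis is described as mainly descriptive, no interval method is given, and the 87% is reported without an interval. The emphasis on intervals in the Discussion also concerns the secondary outcomes.
- *School and village variances cannot be separated.* This is true if each school draws on one village. The article does not say so; pupils of one school may come from several villages.
- *The arm contrasts are unusable.* The article disclaims power and causation, and it makes no go/no-go rule out of an interval excluding the null.

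The simulations have limits too: equal cluster sizes, no adjustment for age, sex or baseline infection, and the log-odds scale where the article reports a cumulative incidence ratio. Covariates may change the residual ICC; unequal cluster sizes would generally worsen coverage.

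**Conclusion.** The concern holds conditionally. Three clusters per arm, a mixed model with arm as a cluster-level effect, and reliance on intervals are all fixed by the article; the z-based interval is the assumption. Under it, error rates for the infection contrast run at two to four times the nominal 5% over latent ICC 0.02 to 0.10 (non-coverage of roughly 10% to 20%). Linear outcomes lie between 10% and 18%, depending on REML or ML. The shortfall vanishes at ICC 0, and no ICC is documented. The consent interval is a supporting point: it would need to be roughly 2.3 times as wide at proportion-scale ICC 0.02, and 3.2 times at 0.05, than one that ignores clustering.

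Severity is moderate. The affected contrasts are secondary outcomes of a feasibility study that already warns against over-reading them, but the warning leaves the interval width uncorrected.

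**What to change.** - **Infection:** base the arm contrast on a two-stage analysis. Adjust for age, sex and baseline infection at child level without the arm term, then compare the six school summaries with a t interval on 4 degrees of freedom.
- **Haemoglobin and Z-scores:** use the same method, or REML with Kenward-Roger degrees of freedom.
- **Random effects:** state how schools map to villages. If each school maps to one village, use a single cluster random intercept.
- **Child-level primary proportions:** state that the confidence intervals allow for clustering by school, and show each school's proportion beside the pooled figure.

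The cost is analysis wording only, with no change to data collection or sample size. The arm-contrast intervals will be about 1.4 times as wide as REML with z, or about 1.7 times as wide as ML with z. That is the precision six clusters can support.
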